## Abstract

**Background:**

Hip replacement surgery is increasingly common due to an ageing population, and rising levels of obesity. The provision of excellent pain relief with minimal side effects is important in order to facilitate patient mobilisation and rehabilitation.

Spinal opioids provide excellent analgesia but are associated with adverse effects. The fascia-iliaca block is an alternative technique which provides analgesia to the nerves innervating the hip. The success of fascia iliaca blocks has been demonstrated to be superior when using ultrasound compared to landmark techniques. However, the clinical benefit of this improvement has yet to be investigated.

The aim of this study is to compare the efficacy and safety of ultrasound guided fascia iliaca block with spinal morphine for hip replacement surgery.

**Methods/Design:**

This study is a randomised, blinded, placebo-controlled, noninferiority trial. Patients scheduled to undergo unilateral primary hip arthroplasty will receive a study information sheet and consent will be obtained in keeping with the Declaration of Helsinki. Patients will be randomised to receive either; (i) Ultrasound guided fascia iliaca block using levobupivacaine, plus spinal anaesthesia with hyperbaric bupivacaine containing no morphine, or (ii) sham ultrasound guided fascia iliaca block performed with sterile saline, and spinal anaesthesia containing hyperbaric bupivacaine and 0.1 mg of spinal morphine.

A total of 108 patients will be recruited. Primary outcome is post-operative morphine consumption in a 24 hour period. Secondary outcomes include; pain scores at 3, 6, 12, 24, 36 and 48 hours, episodes of respiratory depression, hypotension, nausea and vomiting, pruritus, sedation, time to first mobilisation and patient satisfaction.

**Conclusions:**

There are no studies to date comparing ultrasound guided fascia iliaca block with spinal morphine for pain control after hip arthroplasty. If the ultrasound guided fascia iliaca block provides pain relief which is not inferior to spinal morphine, then morphine could be removed from the spinal injection. This could reduce side effects and improve patient safety.

**Trial registration:**

This study has been approved by the West of Scotland Research Ethics Committee 4 (reference no. 10/S0704/43) and is registered with ClinicalTrials.gov (reference no. NCT01217294).

## Background

Hip surgery is increasingly being performed, often in elderly patients with significant co-morbidity [1]. Whilst the optimal anaesthetic technique is yet to be established [2], it is important that side effects are minimised to optimise patient safety and comfort and to facilitate rehabilitation. The main anaesthetic options are general anaesthesia (GA) and regional anaesthesia (RA) or a combination of the two. In a recent systematic review, regional anaesthesia (RA) was demonstrated to reduce post-operative pain, morphine consumption and nausea and vomiting compared to systemic analgesia [3].

Spinal anaesthesia is a RA technique commonly used in many patients undergoing hip arthroplasty [4]. Opioids are frequently added to the spinal anaesthetic in order to prolong and improve post-operative pain relief [5] and are associated with reduced post-operative morphine requirements in patients undergoing hip arthroplasty [6-8]. However, intrathecal opioids are associated with side effects including urinary retention, nausea and vomiting, pruritus and rarely, but most seriously, respiratory depression [9]. Such adverse effects can be uncomfortable for the patient, delay mobilisation, recovery and eventual discharge and occasionally be dangerous [10,11].

In patients undergoing hip arthroplasty peripheral nerve blockade has been shown to improve pain scores and reduce morphine consumption [3]. The fascia iliaca nerve block can provide sensory blockade of the main nerves which supply pain to the hip [12,13]. However, clinical success rates of this block when performed 'blindly' using traditional landmark techniques are variable [14]. Using ultrasound to locate nerves during peripheral nerve blockade has repeatedly been shown to increase success rates, reduce block onset time, increase block duration, reduce volumes of local anaesthetic required and increase patient satisfaction compared to traditional techniques [15-21]. The use of ultrasound guidance in the fascia iliaca plane block has been shown to increase success compared with the landmark technique [22]. In this study however, the clinical benefits of this increased success were not investigated.

Ultrasound guided fascia iliaca block has not yet been evaluated clinically as a method of providing post-operative analgesia following primary hip arthroplasty. We hypothesise that by increasing the success rate of the fascia iliaca block with ultrasound, it will be possible to achieve superior and more reliable analgesia than that obtained using the landmark based technique. The aim of this study is to assess whether the ultrasound guided fascia iliaca plane block can provide comparable post-operative analgesia to spinal morphine for primary hip arthroplasty. If this is the case, spinal opioid could be removed from the spinal anaesthetic. This could potentially reduce troublesome opioid related side effects and have significant safety benefits. The further investigation of this technique will provide a valuable contribution to existing knowledge, and could profoundly change current practice.

## Methods/Design

### Overview

This is a single centre, randomised, blinded, placebo-controlled, non-inferiority study [23]. This study has been approved by the West of Scotland Research Ethics Committee 4 (reference no. 10/S0704/43) and is registered with the ClinicalTrials.gov database (reference no. NCT01217294). This study will be performed in keeping with the requirements of the Declaration of Helsinki.

### Hypothesis

Ultrasound guided fascia iliaca plane block provides post-operative analgesia which is not inferior to that obtained with spinal morphine in patients undergoing primary hip arthroplasty.

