### Objectives and Outcome Measures

This study aims to compare the efficacy and safety of ultrasound guided fasca iliaca block with intrathecal morphine in the provision of post-operative analgesia after primary hip arthroplasty. The primary outcome measure is post-operative morphine consumption in a 24 hour period as self administered using a patient controlled analgesia (PCA) pump. Secondary outcomes include pain scores at 3, 6, 12, 24, 36 and 48 hours, time to 1st morphine administration, episodes of respiratory depression, hypotension, nausea and vomiting scores, pruritus scores, sedation scores, urinary retention, time to first mobilisation and patient satisfaction.

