### Sample Size and Statistical Considerations

In the comparison of ultrasound guided fascia iliaca block with spinal opioid in patients undergoing primary hip replacement, we intend to compare an established technique in widespread practice (spinal morphine) with the less well investigated technique of ultrasound guided fascia iliaca block. The primary outcome of the study is 24 hour morphine consumption. This outcome is used commonly in trials of spinal opioid for hip arthroplasty surgery. Mean 24 hour morphine consumption after hip arthroplasty is reported to lie within the range 10 mg [6] to 30 mg [7] when using 0.1 mg intrathecal morphine. From our own audit data of patients receiving spinal opioid for hip arthroplasty over an 8 month period, mean 24 hour post-operative morphine consumption was 24.6 (SD 17.6) mg which lies within the reported range described above [6,7].

In order to calculate sample size, we used a method suggested for non-inferiority trials [23,24]. For this we made the following assumptions. Type 1 error (α) was set at 0.05; Type 2 error (β) at 0.8; and Z numbers based on one-tailed testing. We considered a difference between groups (δ*) of greater than 10 mg of morphine to be clinically significant. 10 mg of morphine equates to one subcutaneous dose of morphine commonly used in post-operative analgesia pain protocols [25].

The expected difference between the Control (spinal morphine) and Treatment (ultrasound guided fascia iliaca) groups (δ) is more difficult to estimate. To date, there is only one published trial looking at 24 hour post-operative morphine consumption after fascia iliaca block for hip arthroplasty, although this was performed with the landmark technique alone and did not employ ultrasound [13]. In this study, mean 24 hour post-operative morphine consumption in the fascia iliaca group was 23 mg. Therefore, there is a 1.6 mg difference between the mean 24 hour morphine consumption obtained from our audit data of patients receiving spinal morphine, and that obtained in a study looking at patients receiving fascia iliaca block for hip arthroplasty [13]. Thus, the number of patients required to adequately power this study is 108.

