The null Hypothesis (H0) for this non-inferiority study is that the experimental treatment (ultrasound guided fascia iliaca block) is in fact inferior to the established treatment (spinal morphine) by more than the clinically significant amount (δ*). If H0 is rejected, the alternative hypothesis is that ultrasound guided fascia iliaca block is not inferior to IT opioid.

The study will be performed using both intention to treat and "as treated" analyses. In the intention to treat analysis, patients will be considered failures if they require general anaesthesia, or were unable to receive randomised treatment for any other reason. In the "as treated" analysis, only data from patients completing randomised treatment will be analysed.

Secondary data analyses will be carried out on all secondary outcomes. These will be compared between groups using t-test, and Mann-Whitney, or Chi-squared tests as appropriate.

It is anticipated that recruitment for this study will take between 12 and 18 months to complete if 1 to 2 patients are enrolled each week, using one surgeon to reduce surgical variability. Data collection for each patient will occur during the first 48 hours post-operatively and at a routine 6 week follow up appointment. No further follow up will be routinely arranged. Any patients requiring specific follow up will have this arranged on an individual basis.

We recognise that while this study is powered for the primary outcome, it is not powered for the secondary outcomes. However, the data we collect in this study will provide useful information for further studies looking specifically at these outcomes.

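### The planned conclusion is non-inferior analgesia, but the only non-inferiority rule is on 24-hour morphine consumption, and the difference tests planned for pain cannot fill the gap

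*Protocol article*

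**What the plan says.** All references are to the protocol article.

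- **Claim.** The Hypothesis section reads: "Ultrasound guided fascia iliaca plane block provides post-operative analgesia which is not inferior to that obtained with spinal morphine". The last paragraph of the Background sets the aim as comparable analgesia. The Abstract's Conclusions say that if the block "provides pain relief which is not inferior to spinal morphine, then morphine could be removed from the spinal injection".
- **Outcome tested.** Under Objectives and Outcome Measures: "The primary outcome measure is post-operative morphine consumption in a 24 hour period as self administered using a patient controlled analgesia (PCA) pump".
- **Margin.** Under Sample Size and Statistical Considerations: "We considered a difference between groups (δ*) of greater than 10 mg of morphine to be clinically significant". No margin is given for any other outcome.
- **Decision rule.** The same section states: "If H0 is rejected, the alternative hypothesis is that ultrasound guided fascia iliaca block is not inferior to IT opioid". H0 is defined by the morphine margin alone.
- **Pain.** Under Objectives and Outcome Measures: "Secondary outcomes include pain scores at 3, 6, 12, 24, 36 and 48 hours". The analysis of all secondary outcomes is: "These will be compared between groups using t-test, and Mann-Whitney, or Chi-squared tests as appropriate". The section adds that "while this study is powered for the primary outcome, it is not powered for the secondary outcomes".

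**The concern.** The claim and the test concern different things. The claim is about pain relief, and the test is about how much morphine patients chose to take. PCA consumption reflects pain, side effects and willingness to press the button together. Two groups can therefore use similar amounts of morphine while one is in more pain. Meeting the 10 mg margin establishes non-inferior consumption. It establishes non-inferior analgesia only with the further information that pain is not worse.

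The one planned pain analysis cannot supply that information. T-tests, Mann-Whitney tests and Chi-squared tests look for a difference, and failing to find one in an unpowered comparison is not evidence that pain is no worse. At stake is what a positive trial may say, because the suggestion that spinal morphine could be omitted is tied to pain relief and not to consumption.

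**Working it through.** **Inputs from the protocol article (Sample Size and Statistical Considerations).** Margin 10 mg; SD 17.6 mg; expected difference 1.6 mg; one-sided alpha 0.05; power 0.80 (the text gives 0.8 as the type 2 error, read here as power); total 108 patients. The allocation ratio is not stated; 1:1 is assumed, giving 54 per arm.

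**Inputs assumed, because the article gives no pain scale, SD or threshold.** 0-10 scale, SD 2, 2.5 or 3, a true worsening of 1 point, one time point.

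**1. Reproduce the sample size.** n per arm = 2 × [SD × (z0.95 + z0.80) / (margin − difference)]² = 2 × [17.6 × (1.645 + 0.842) / (10 − 1.6)]² = 54.3, or 108.6 in total, against the stated 108 (110 if each arm is rounded up). The formula reproduces the figure, so the whole sizing rests on morphine.

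**2. What passes the rule.** The standard error is 17.6 × √(2/54) = 3.39 mg. The one-sided 95% limit lies below 10 mg when the observed excess in the block arm is under 10 − 1.645 × 3.39 = 4.4 mg. Pain scores do not enter this calculation.

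**3. What a difference test on pain can show.** SE = SD × √(2/54) = 0.385, 0.481 and 0.577 for SD 2, 2.5 and 3. The normal approximation to power is Φ(1/SE − 1.96):

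| SD | Power | Chance of missing 1 point | Same, by t-test | Observed worsening still non-significant (1.96 × SE) |
|---|---|---|---|---|
| 2 | 74% | 26% | 27% | up to about 0.75 |
| 2.5 | 55% | 45% | 46% | up to about 0.94 |
| 3 | 41% | 59% | 60% | up to about 1.13 |

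**4. What a confidence limit on the same data shows.** The one-sided 95% half-width is 1.66 × SE = 0.64, 0.80 and 0.96. If 1 point were the threshold, the limit would exclude it only when the observed worsening was below 1 − 0.64 = 0.36, 1 − 0.80 = 0.20 or 1 − 0.96 = 0.04. At SD 2.5, any observed worsening between 0.20 and about 0.94 would be non-significant and would still leave a 1-point worsening possible. The two readings of the same data differ over that whole range.

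**5. Power of the limit to exclude a worsening.** With no true pain difference, power is Φ(threshold/SE − 1.645). For a 1-point threshold this is 83%, 67% and 54% (SD 2, 2.5, 3). For 1.5 points it is 99%, 93% and 83%.

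**The case against.** The strongest reply is that the protocol states openly how it measures analgesia. It defines inferiority in milligrams of morphine and notes that this outcome is common in trials of spinal opioid for hip arthroplasty. Both arms have the same PCA regimen and patients are blinded, so markedly worse pain would usually raise consumption. Pain scores, time to first morphine and satisfaction are all collected, so readers could see worse pain. The remark about omitting spinal morphine is conditional. All of this stands and limits the weight of the point, but none of it puts a pain condition behind a conclusion worded as pain relief.

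It can also be said that confidence limits for secondary outcomes belong in an analysis plan that is not shown. That is fair for the details. The mismatch between the stated hypothesis and the stated decision rule is in the article itself.

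Three stronger readings are tempting and are not supported:

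- A reader might infer that the investigators will treat a non-significant pain test as proof of comparable pain. No section says so. The article states that the secondary outcomes are unpowered and will inform further studies.
- A reader might infer that side effects which discourage PCA use would bias the trial towards the block. The Background and the Risk Benefit Assessment attribute nausea, vomiting, pruritus and respiratory depression to intrathecal morphine, which only the control arm receives. Reduced demand there would lower control consumption and make non-inferiority harder to show. The documents give no direction.
- A reader might infer that a second, formal pain margin is obligatory. That is a debatable choice of endpoint. The article gives no such margin, and the cost could be large. Taking 80% power on morphine and independence for illustration, the chance of meeting both limits is 0.80 × 0.83 = 66% (SD 2) down to 0.80 × 0.54 = 43% (SD 3) for 1 point, and 0.80 × 0.99 = 79% down to 0.80 × 0.83 = 66% for 1.5 points. Positive correlation would raise these figures.

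**Conclusion.** The point holds as a mismatch between claim and test. A positive result under the stated rule would establish non-inferior 24-hour morphine consumption. It would not by itself establish non-inferior analgesia, and the planned difference tests on pain could not make up the shortfall. The primary outcome, its margin and the sample size are not challenged by this point.

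The miss rate of roughly 27% to 60% is illustrative. It depends on the assumed 0-10 scale, SD of 2 to 3, 1-point worsening, 1:1 allocation and a single time point. The logical gap does not depend on those assumptions. The documents do not support saying that the trial is biased towards the block, or that its authors plan to misread a non-significant pain test.

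**What to change.** Keep 24-hour morphine consumption as the primary outcome and leave its test unchanged. Then:

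1. State the non-inferiority conclusion as non-inferior 24-hour morphine consumption.
2. Report the pain score differences, block minus spinal morphine, with confidence limits, and do not rely on non-significant difference tests.
3. Before unblinding, fix the pain comparison to be used and the worsening judged clinically important. Use the wider wording, analgesia not inferior, only if the confidence limits exclude that worsening.

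This needs no extra patients or data. The cost is a narrower default claim. The wider claim becomes harder to reach, possibly substantially so if the pain threshold is strict. If the investigators do not want that burden, steps 1 and 2 alone are enough, and the conclusion stays with morphine consumption.

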### Objectives and Outcome Measures

This study aims to compare the efficacy and safety of ultrasound guided fasca iliaca block with intrathecal morphine in the provision of post-operative analgesia after primary hip arthroplasty. The primary outcome measure is post-operative morphine consumption in a 24 hour period as self administered using a patient controlled analgesia (PCA) pump. Secondary outcomes include pain scores at 3, 6, 12, 24, 36 and 48 hours, time to 1st morphine administration, episodes of respiratory depression, hypotension, nausea and vomiting scores, pruritus scores, sedation scores, urinary retention, time to first mobilisation and patient satisfaction.

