### Randomisation

A computer generated allocation sequence (in permuted blocks) will be created by an independent operator who is not directly involved with the study. Once created, the allocation sequence will be kept in a secure locked drawer making it inaccessible to all study personnel. Allocation concealment will be achieved using sequentially numbered sealed envelopes which are opaque when held to the light. When a patient is enrolled in the study, an administrator working within the Glasgow University Academic Unit of Anaesthesia will be contacted and asked to give the next numbered envelope to the anaesthetist who will make up the medications used in the study. The administrator will record the patient's details and the number of the envelope assigned to that patient. The allocation sequence will be accessed only when study data collection is complete or in any instance where unblinding of the study is thought to be essential in the provision of appropriate patient care.

Patients in the *Fascia Iliaca Group *will receive; spinal anaesthesia with hyperbaric bupivacaine at a dose between 10 and 15 mg, adjusted based on patient height and weight at the discretion of the attending anaesthetist, with no spinal morphine (0.1 ml sterile saline will be administered in its place). Ultrasound guided fascia iliaca block using 2 mg/kg levobupivacaine diluted to a total of 40 ml with sterile saline.

Post-operative analgesia will include Paracetamol 1 g four times daily and patient controlled analgesia (PCA) with morphine (1 mg bolus, 5 minute lockout period).

Patients in the *Spinal Morphine Group *will receive; spinal anaesthesia with hyperbaric bupivacaine as above, and with the addition of intrathecal morphine 100 micrograms (0.1 ml). "Sham" ultrasound guided fascia iliaca injection with 40 ml of sterile saline. Post-operative analgesia in the same manner as in the *Fascia Iliaca Group*.

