### Postoperative management

After surgery, patients will be taken to the recovery room and monitored according to standard hospital policy. Pain will be treated, if required, with intravenous morphine every 5 - 10 min as directed by nursing staff. Patients will be familiarised with the Patient Controlled Analagesia (PCA) device and discharged once recovery room discharge criteria have been met. Patients will remain on oxygen for at least 24 hours and whilst receiving PCA morphine as is routine in our unit. Naloxone will be prescribed for sedation or respiratory depression as specified on the PCA protocol.

After a 48 hour period, data regarding pain scores, nausea, itch, sedation and hypotension will cease being collected as detailed in the primary and secondary outcomes. The investigator who collects the data will be blinded as to the nature of the anaesthetic administered. The time to first mobilisation will be assessed and the patient will continue to be monitored by physiotherapy staff until discharge. Any serious adverse events will prompt follow up. Patients will be seen routinely at 6 weeks following discharge by the arthroplasty specialist nurse. Symptoms of nerve damage will be actively sought at this consultation. Patients will be asked to rate their level of satisfaction with post-operative analgesia at both 48 hour and 6 week time points.

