### Data Collection

Data will be obtained from copies of the anaesthetic record, recovery room observation chart, PCA chart, ward observation chart and drug prescription chart. These charts will be reviewed after the first 48 hour post-operative period by a member of the research team. The researcher will be blinded to the anaesthetic technique used. All documentation relating to the study will be stored in an anonymised case report file unique to each patient. These case report files will be archived in a locked facility for a period of 10 years.

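### The primary outcome is defined as PCA morphine only, which leaves out nurse-given recovery morphine, while other sections name it without that limit; unequal recovery use would bias the non-inferiority test

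*Protocol article*

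**What the plan says.** Objectives and Outcome Measures gives the only operational definition of the primary outcome: "post-operative morphine consumption in a 24 hour period as self administered using a patient controlled analgesia (PCA) pump". Two other places name it more broadly. The Methods/Design paragraph of the abstract has "Primary outcome is post-operative morphine consumption in a 24 hour period", and Sample Size and Statistical Considerations has "The primary outcome of the study is 24 hour morphine consumption". Neither mentions the pump.

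Postoperative management describes a second source of morphine, in the recovery room: "Pain will be treated, if required, with intravenous morphine every 5 - 10 min as directed by nursing staff". Patients are introduced to the PCA device during the same stay. No section says whether the nurse-given morphine counts towards the primary outcome, or when the 24 hours start.

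Data Collection lists the "recovery room observation chart, PCA chart, ward observation chart and drug prescription chart" among the sources, so the trial already gathers the records on which recovery morphine would be expected to appear.

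**The concern.** Nurse-given recovery morphine is post-operative and falls early in the first 24 hours, but it is not self-administered. An analyst who follows Objectives and Outcome Measures leaves it out. One who follows the abstract or the sample size section counts it. The same patients could then give two different primary results.

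The design makes this matter. The hypothesis is about post-operative analgesia, not pump use, and the test asks whether the block arm's mean exceeds the control mean by less than 10 mg. A patient whose block works poorly may be treated in recovery, and on the PCA-only definition that morphine contributes nothing. If this happens more often in the block arm, the observed difference shrinks towards a non-inferiority claim.

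**Working it through.** **Inputs from Sample Size and Statistical Considerations.** SD 17.6 mg and mean 24.6 mg (audit data), margin 10 mg, expected difference 1.6 mg, one-sided α 0.05, total 108. The text has "Type 1 error (α) was set at 0.05; Type 2 error (β) at 0.8"; I read the second figure as power 0.8, because a literal β of 0.8 gives only 6 per arm. Equal allocation is my assumption, since the article states no ratio.

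**The plan's own figure.** n per arm = 2 × [17.6 × (1.645 + 0.842) / (10 − 1.6)]² = 54.28, or 108.57 in total (110 if each arm is rounded up). The stated 108 is reproduced to within 2 patients, so the sample size arithmetic is not at issue here.

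**Effect of leaving out recovery morphine.** Let D be the true difference in mean total morphine (block minus spinal morphine) and h the net mean excess of recovery morphine in the block arm. The PCA-only difference is then D − h. Any effect of early rescue on later PCA demand is already contained in D and needs no extra term.

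- Standard error with 54 per arm: 17.6 × √(2/54) = 3.39 mg, taken as the same for PCA-only and total morphine.
- Non-inferiority is declared if the observed difference is below 10 − 1.645 × 3.39 = 4.43 mg.
- P(declare) = Φ((10 − (D − h))/3.39 − 1.645). With D at the margin of 10 mg this becomes Φ(h/3.39 − 1.645).

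| h (mg, assumed) | P(declare non-inferiority) when D = 10 mg |
|---|---|
| −2 | 1.3% |
| −1 | 2.6% |
| 0 | 5.0% |
| 1 | 8.9% |
| 2 | 14.6% |
| 3 | 22.4% |

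The article gives no value for h. To give it scale: if an extra 10%, 20% or 30% of block patients each received 10 mg in recovery, h would be 1, 2 or 3 mg. Negative values mean more recovery morphine in the spinal morphine arm, which makes the PCA-only test conservative.

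**The case against.** The strongest reply is that the bias is conditional and nothing in the article establishes the condition. Recovery morphine is given only if required, and both arms receive spinal bupivacaine, so early need may be low and similar in the two arms. The table also places the true difference at the margin, whereas the plan expects 1.6 mg; at that value a non-inferiority claim would be correct under either definition. All of this stands. It limits what can be said about size and direction.

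A second reply is that the broader wording is merely a short label for the same endpoint, or that a condensed article leaves such detail to the full protocol. This stands in part. A short label need not be a rival definition. But the article does fix a definition, and that definition excludes a morphine source which the article itself describes. If the broad wording was the one intended, the explicit definition is wrong and still has to change.

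A reader might also infer that early block failure would go unseen. The article does not support that: the 3 hour pain score and time to first morphine are secondary outcomes and could show it, although they do not enter the non-inferiority test. Nor does it support a claim that other opioids go uncounted, because apart from recovery morphine the stated regimen is paracetamol and PCA morphine.

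**Conclusion.** The point holds as a defect in the endpoint definition and should be fixed. As written, the operational definition leaves nurse-given recovery morphine out of the non-inferiority comparison, and the abstract and sample size section do not carry the same limit.

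A reader might conclude that the trial is biased towards non-inferiority. The article does not show that. Such bias needs more recovery morphine in the block arm; equal use gives none, and more use in the control arm reverses it. The rise in the false-claim rate from 5% to about 9% to 22% is an illustration. It rests on an assumed net excess of 1 to 3 mg, a true total difference at the 10 mg margin, SD 17.6 mg, 54 per arm and a normal approximation. What does not depend on those assumptions is that each mg of net excess moves the estimate by 1 mg, and that two readings of the primary outcome are open.

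**What to change.** Define the primary outcome identically in the abstract, Objectives and Outcome Measures, and Sample Size and Statistical Considerations: total post-operative morphine over 24 hours from a stated start time that covers the recovery stay, summing nurse-given recovery morphine and PCA morphine, plus any other opioid in morphine equivalents if one is given. Keep PCA-only morphine as a sensitivity analysis. State whether the audit mean and SD (24.6 and 17.6 mg) included recovery morphine.

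The cost in data is small, since the recovery room, PCA and drug prescription charts are already collected; no extra visits are needed. The sample size inputs do need checking, because the SD of total morphine may be slightly larger than that of PCA morphine alone. With the plan's other inputs unchanged and each arm rounded up, the total is 110 at SD 17.6 mg; assumed SDs of 18.5 and 20 mg would give 120 and 142. If the audit figures already include recovery morphine and the expected difference stands, the basis for 108 is unchanged.
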